### Description of the control condition

Comparable to the standard of care, the control condition consisted of a standard set of safety strategies with an emphasis on referral resources. For comparability to the intervention arm, content was delivered in the form of an app, staff were present to assist women in understanding material, and participants given the option to return to the study office to review.

### Post-intervention assessment

Following receipt of intervention or control app content, participants completed a brief exit survey facilitated by the tablet. They completed a brief upset screener. All participants were offered a small grocery item as appreciation for their participation, as well as transport reimbursement.

### Referrals

All participants were offered referrals for IPV-related medical, psychosocial, or economic support. Those interested in referrals were directed to a Referral Lead; Referral Leads were blinded to intervention status and separate from the data collectors. Participants were offered contact information and the option for a “warm” facilitated referral to reduce barriers to care for participants in both conditions. Participants had the option to return to the study center to review their safety plan and referral list prior to three-month follow-up visit.

### 3-month follow-up data collection and retention

Participants were contacted for 3-month follow-up data collection at their original study office. Following refresher consent, survey data collection procedures were identical to those at baseline, specifically tablet-based data collection in English or Swahili language, lasting approximately 30–45 min, and with provision of resource referrals, transportation remuneration, small grocery item, and universal upset screener (Fig. 2). Intervention arm participants were also given the option for an in-depth interview at a later time period. Control participants were given the option to complete the myPlan Kenya app following survey data collection. The eligibility window for follow-up data collection began one week prior to the three-month anniversary of baseline through one month afterwards. A participant could be called up to five times; if such calls proved unsuccessful the research team attempted to reach her via her two provided alternate contacts. Participants were deemed ineligible for follow-up if they had moved out of the study area or if they were temporarily traveling and would not return by the end of the follow-up period.

**Fig. 2 Fig2:**
[figure not shown]
Schedule of enrollment, interventions, and assessments for myPlan Kenya

### In-depth interview

Intervention participants who completed the baseline and follow-up surveys were eligible for a 30-min in-depth interview (IDI). Purposive sampling ensured a range of violence experiences and study sites (*n* = 30). Semi-structured interview guides focused on participant’s experiences with and recommendations for the intervention. Interviews were audiorecorded, transcribed verbatim, and translated to English language for analysis.

## Risk & safety

### Participant safety

Steps to enhance participant safety and confidentiality included baseline and refresher oral informed consent. At each session, a data collector explained procedures, answered questions, and signed as a witness to oral consent. All consent, survey data collection, app, and referrals were conducted individually in a private setting at the respective study site office.

All field and research team members completed human subjects and ethical training prior to study implementation. Formative and RCT training emphasized ethics specific to violence research. Precautions included skipping questions as necessary, monitoring reactions, and procedures for pausing and concluding interviews in case of severe upset or other adverse events.

### Study team safety

Study team precautions comprised conducting data collection during daylight hours, traveling to recruitment and data collection events in pairs, and using concealed bags for study material storage.

Buy-in from local communities including local chiefs was essential to success and safety of participants and staff. All local chiefs were contacted during the formative phase to introduce the app and study procedures, and solicit feedback. As part of recruitment, community presentations such as Parent-Teacher Association meetings, served to engage local community members in the study and solicit input.

### Contingency planning & monitoring for potential challenges

Throughout training, data collectors were given ample opportunity to contingency plan for a wide array of potential adverse events, in line with best practices for violence research [43]. Provisions were made to ensure immediate contact with the research team for swift response and timely IRB notification for any potential adverse events.

Twice weekly calls with the JHU team, and research support presence, including an on-site research fellow, throughout data collection facilitated field communication, protocol fidelity, monitoring for potential adverse events, and technical support. Technology issues were identified and resolved in real time, facilitated by online reports with screenshots to enable rapid troubleshooting. Over the seven-month data collection period, three site visits were conducted for the purposes of auditing data collection processes and documents, and field implementation observation. Extensive field notes submitted daily monitored the risk for social harm and adverse events, so as to enable rapid team communication and response.

### Data privacy measures

Identifying information to support retention included name (or pseudonym), phone number, and the names and phone numbers of two alternative contacts. All identifiers were stored in a separate password-protected database and only available to the recruitment team for follow-up calls. Survey data, app data and subsequent downloads were stored on a secure cloud server, as were IDI audio and transcripts.

## Data analyses

Prior to analyses, data quality will be examined through descriptive statistics, including tabulations and distributions to assess missingness. Imputation will be used for variables with missingness < 10%. Differences in intervention and control groups will be assessed for outcomes and potential confounding variables using Chi-square tests (categorical variables) and t-tests/ANOVA (continuous variables). Significance will be set at 5%. All analyses will account for site and within-person clustering. Attrition analysis comparing key demographics and baseline indicators across those lost-to-follow up with those retained will identify potential biases in the final retained sample.

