### Randomization to intervention or control condition

Following tablet-based baseline survey data collection, women were randomized to either the control or intervention arm within the app itself, stratified by study site (1:1 allocation); following randomization participants were seamlessly directed to either the control or the intervention app. The tablet further eased data collection given recording of all consent, survey data, and app measures, as well as analytics on time-to-completion and missingness of data. Intervention participation took approximately 30–45 min, whereas the control condition was limited to 10–20 min.

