### Intervention efficacy

All analyses will be performed using intent-to-treat principles. Primary analysis uses a differences-in-differences approach to compare differences between baseline and 3-month follow-up by intervention group. Random effects logistic and linear regression models will be created, including study arm, pre/post status and their interaction term (study arm*pre/post status). Interaction terms significant at *p*-value < 0.05 will indicate a significant intervention effect.

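### For continuous outcomes measured at baseline and 3 months, the difference-in-differences model is valid but inefficient; adjusting for the baseline value would cut variance by about 30% (assumed correlation 0.4) at no cost

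*Protocol article*

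**What the plan says.** In the protocol article, under Intervention efficacy: "Primary analysis uses a differences-in-differences approach to compare differences between baseline and 3-month follow-up by intervention group". The random-effects linear and logistic models are described as "including study arm, pre/post status and their interaction term", and the interaction tested at 0.05 is the intervention effect. Study arm enters as a free term, so each arm has its own baseline mean.

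Under Data analyses, among steps that begin "Prior to analyses, data quality will be examined through descriptive statistics, including tabulations and distributions to assess missingness", the plan adds: "Differences in intervention and control groups will be assessed for outcomes and potential confounding variables using Chi-square tests" for categorical variables, and t-tests/ANOVA for continuous ones. The level is 5%. The same paragraph states: "All analyses will account for site and within-person clustering".

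Under Randomization to intervention or control condition, women are allocated after the baseline survey, "stratified by study site (1:1 allocation"). Under Statistical power, the trial has 175 women per arm.

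**The concern.** Arms are formed at random after the baseline survey, so any baseline difference between them is chance. A change-score contrast removes that difference in full, although part of it would have disappeared by 3 months through regression to the mean. The contrast therefore over-corrects. In a trial where one arm happens to start worse on an outcome, that arm will appear to improve more even if the app does nothing.

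A 5% test of balance is a poor guard. Its null hypothesis is true by design, and it passes differences large enough to matter. A non-significant result would reassure the reader while the estimate remained shifted.

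At stake are precision and the credibility of the estimate in the one trial that is run. The plan models many of its scales continuously, so the loss recurs across outcomes.

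**Working it through.** **Inputs.** From the document: 175 per arm, 5% level, model terms arm, pre/post and their product. Assumed: two-sided tests, equal outcome variance at both times, complete data, and baseline to 3-month correlation r = 0.4 with range 0.3 to 0.6. The article gives no correlation.

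**1. What the balance test lets through.** The largest unflagged difference is 1.96 × √(2/n) SD.
- n = 175: 1.96 × √(2/175) = 0.21 SD.
- n = 149 (15% attrition): 1.96 × √(2/149) = 0.23 SD.

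**2. Variance.** Let σ² be the outcome variance in each arm at each time.
- Change score, per woman: 2(1 − r)σ².
- Baseline-adjusted 3-month value: (1 − r²)σ².
- Ratio: (1 − r²) / [2(1 − r)] = (1 + r)/2.

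| r | Ratio | Variance saved |
|---|---|---|
| 0.3 | 0.65 | 35% |
| 0.4 | 0.70 | 30% |
| 0.6 | 0.80 | 20% |

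**3. Shift from a chance imbalance.** Let z be the baseline arm difference in its own SE units. Given z, the change-score estimate is expected to move by (1 − r)z in those units, against the direction of the imbalance. Its SE is √[2(1 − r)], so the shift is z√[(1 − r)/2] of its own SE, and the conditional SD of the test statistic is √[(1 + r)/2].

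At r = 0.4 and z = 1.5 (baseline p = 0.13, not flagged):
- shift = 1.5 × √0.3 = 0.82 SE; conditional SD = √0.7 = 0.837;
- upper tail: 1 − Φ[(1.96 − 0.822)/0.837] = 1 − Φ(1.36) = 0.087; the other tail is about 0.0004;
- conditional two-sided error = 8.7%.

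| Baseline z (p) | r = 0.3 | r = 0.4 | r = 0.6 |
|---|---|---|---|
| 0 (1.00) | 1.5% | 1.9% | 2.8% |
| 1.5 (0.13) | 9.2% | 8.7% | 7.6% |
| 1.9 (0.057) | 15.0% | 13.6% | 10.8% |

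Averaged over the normal distribution of z, the error is 5.0% for each r. With the baseline value as a covariate it is 5% at every z.

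**The case against.** The strongest defence is that nothing in the plan is invalid. Difference-in-differences is unbiased over randomisations and holds its 5% level. Error rates above 5% arise only by conditioning on an unlucky baseline, and with perfect balance the error falls to about 2%. This stands. The gain is in precision and in freedom from conditional shift.

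The error and variance figures also describe the change-score model and would be the same if no balance test were run. That stands too, so the tests are a secondary matter here.

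A reader might infer that the tests select covariates, making adjustment data-driven. The article does not say so: no sentence makes adjustment depend on a test result, and the model terms are fixed under Intervention efficacy. Even if adjustment did follow a significant test, the unconditional error of an otherwise unadjusted follow-up comparison would be 4.8%, 4.3% and 3.6% at assumed correlations of 0.3, 0.5 and 0.7, which is conservative rather than inflated.

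A reader might also take the tests to be baseline tests as a matter of fact. That is the natural reading for confounding variables, but the sentence does not use the word and could cover follow-up outcomes.

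Site is already accounted for in the plan. A list of further prognostic covariates is commonly left to a full analysis plan, so its absence is no fault.

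One defence fails: that difference-in-differences already deals with baseline. It includes the baseline value but, with a free arm term, gives it a fixed weight of one instead of the weight the data support.

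**Conclusion.** The point holds as a free improvement. For continuous outcomes measured at both times, the planned contrast uses the baseline less efficiently than it could: about 30% more variance than needed is carried, in the sense that adjustment would remove that share, at an assumed r of 0.4 (20% to 35% for r from 0.6 to 0.3). An unflagged imbalance at z = 1.5 moves the estimate by about 0.8 of its SE at r = 0.4. The 5% between-arm tests, read as baseline tests, would not catch it.

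The figures assume equal variances and complete data; with dropout, the equivalence to a change score is only approximate. They do not cover the binary IPV outcome on which the trial is powered and which falls under the logistic model. The point does not apply to safety preparedness, which the Primary outcomes section describes as assessed immediately after the intervention or control condition.

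It would be wrong to conclude that the trial's type I error is inflated or that its sample size needs to change.

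**What to change.** For each continuous outcome measured at baseline and 3 months, state one of two equivalent approaches in advance:
- analyse the 3-month value with arm, site and the baseline value of that outcome as covariates; or
- keep the longitudinal model but drop the free arm term, so that both arms share one baseline mean and the arm-by-time term remains the effect. This stays closest to the present plan.

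Apply the chosen approach whatever imbalance is seen. As a minor companion, present the baseline table by arm without p-values, and say plainly which time point the between-arm tests were meant for.

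The cost is a change of analysis wording. The baseline values are already collected on the tablet, and the sample size is unaffected.

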### Intervention efficacy

All analyses will be performed using intent-to-treat principles. Primary analysis uses a differences-in-differences approach to compare differences between baseline and 3-month follow-up by intervention group. Random effects logistic and linear regression models will be created, including study arm, pre/post status and their interaction term (study arm*pre/post status). Interaction terms significant at *p*-value < 0.05 will indicate a significant intervention effect.

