## Randomized controlled trial methods

### Design

This trial is designed as a randomized, controlled, participant-blinded superiority trial with two parallel groups (1:1 allocation ratio), with primary end points of safety preparedness, decisional conflict (e.g. clarity of values, knowledge), use and helpfulness of safety strategies, and IPV.

We hypothesized women in the myPlan Kenya safety decision app group would have increased safety preparedness, reduced decisional conflict about safety priorities, increased helpfulness and use of safety behaviors, and reduced IPV at three-months post-baseline in comparison to the control group.

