### Statistical power

As decisional conflict estimates were unavailable for target population, the study powers on IPV; 2014 Kenya national data estimate 39% lifetime IPV prevalence for women [12]. Setting alpha = 0.05 and power to .80, a study with 175 intervention participants and 175 controls will find a significant difference between the groups if 25% of women experience violence in the intervention group compared to 39% in the control group [57]. If attrition rate is 15%, we will be able to detect significant difference if 24% of the intervention group experiences IPV.

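### The stated 80% power belongs to a one-time-point comparison of two proportions, while the primary test is an arm-by-time interaction whose power rests on a baseline IPV rate and a within-person correlation that the protocol does not give

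*Protocol article*

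**What the plan says.** **Primary test.** Under Intervention efficacy: "Primary analysis uses a differences-in-differences approach to compare differences between baseline and 3-month follow-up by intervention group". The models are random-effects logistic and linear regressions with arm, pre/post status and their product. A product term below the 5% level is the criterion for an intervention effect.

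**Power.** Under Statistical power, the trial is sized on IPV: "Setting alpha = 0.05 and power to .80, a study with 175 intervention participants and 175 controls" is said to give a significant difference "if 25% of women experience violence in the intervention group compared to 39% in the control group". The 39% has its own source: "2014 Kenya national data estimate 39% lifetime IPV prevalence for women". The attrition version reads "If attrition rate is 15%, we will be able to detect significant difference if 24% of the intervention group experiences IPV". No baseline rate, change from baseline or within-person correlation appears.

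**Design facts that bear on this.** Randomisation comes after the baseline survey and is "stratified by study site (1:1 allocation"). Under Data analyses: "All analyses will account for site and within-person clustering". Entry requires physical or sexual IPV, or fear of the partner, in the last three months (Recruitment of participants). Safety preparedness, one of the primary outcomes, is described only straight after the app session, and its items ask about the material just seen (Primary outcomes).

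**The concern.** The article fixes both the test and the power, and they do not belong together. A comparison at follow-up carries the sampling error of two proportions. The interaction carries that of four, partly offset by the correlation between a woman's two answers. Because randomisation follows the baseline survey, the expected baseline difference is zero, so subtracting the observed one removes no bias. It helps precision only if the within-person correlation is high enough.

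Since significance of the interaction is the stated criterion, a real 14-point reduction in IPV could be reported as no effect more often than the one time in five that the power section implies. For safety preparedness there is no pre-intervention value, so the baseline-to-3-month interaction cannot be fitted at all.

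**Working it through.** **1. The plan's own figure.** Two-sided alpha 0.05, pooled variance under the null, no continuity correction:

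z = [|p1 - p2| - 1.96·sqrt(2·p̄·(1 - p̄)/n)] / sqrt[(p1q1 + p2q2)/n], power = Φ(z).

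- n = 175, 39% vs 25%: z = 0.857, power 80.4% (174 per arm suffice for 80%).
- n = 175 × 0.85 ≈ 149, 39% vs 24%: z = 0.838, power 79.9%.

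Both stated figures reproduce. A continuity-corrected version (188 per arm, 77%) and a one-sided version (137 per arm, 88%) do not. The stated power is therefore that of one proportion per arm at one time point.

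**2. Power of the interaction for the same effect.** From the article: 39% vs 25% at follow-up, n = 175 per arm. Assumed, because the article gives no values: a common baseline rate p0 and a baseline-to-follow-up correlation ρ.

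- Risk-difference scale: v = sum over arms of [p0q0 + p1q1 - 2ρ·sqrt(p0q0·p1q1)], power = Φ(0.14/sqrt(v/n) - 1.96).
- Logit scale (marginal): v = sum over arms of [1/(p0q0) + 1/(p1q1) - 2ρ/sqrt(p0q0·p1q1)]. The effect is ln(0.39/0.61) - ln(0.25/0.75) = 0.651, and power = Φ(0.651/sqrt(v/n) - 1.96).

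Example at p0 = 39%, ρ = 0.3, risk-difference scale: the control arm gives 0.2379 + 0.2379 - 0.1427 = 0.3331, and the intervention arm 0.2379 + 0.1875 - 0.1267 = 0.2987. So v = 0.6317, SE = sqrt(0.6317/175) = 0.0601, 0.14/0.0601 = 2.33, and power = Φ(0.37) = 64%.

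Baseline 39%, 39% vs 25% at follow-up:

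| ρ | Risk diff., n=175 | Logit, n=175 | Risk diff., n=149 | Logit, n=149 |
|---|---|---|---|---|
| 0 | 50% | 53% | 44% | 47% |
| 0.1 | 54% | 57% | 48% | 51% |
| 0.2 | 59% | 62% | 52% | 55% |
| 0.3 | 64% | 68% | 58% | 61% |
| 0.4 | 71% | 75% | 64% | 68% |
| 0.5 | 79% | 82% | 72% | 75% |
| 0.6 | 87% | 89% | 81% | 84% |

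The random-intercept logistic model that the plan names, evaluated at 175 per arm on expected counts, gives 56%, 61%, 66%, 73%, 80% and 87% for ρ = 0.1 to 0.6, in line with the table. On the risk-difference scale the interaction reaches 80% at ρ of about 0.52.

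**3. Higher baseline rates.** Two binary variables with unequal prevalences cannot be strongly correlated. For p0 above p1 the maximum is ρ = p1(1 - p0)/sqrt(p0q0·p1q1). With the plan's follow-up rates and n = 175:

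| Baseline | Cap, control | Cap, intervention | Logit power, ρ=0 to cap | Risk-diff. power, ρ=0 to cap |
|---|---|---|---|---|
| 60% | 0.65 | 0.47 | 53-86% | 49-84% |
| 70% | 0.52 | 0.38 | 51-76% | 52-78% |
| 80% | 0.40 | 0.29 | 45-62% | 57-75% |
| 90% | 0.27 | 0.19 | 33-40% | 66-76% |

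From 70% upwards no attainable correlation brings either scale to 80%.

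**4. Baseline adjustment against difference-in-differences, continuous outcomes.** With equal variance σ² at both visits, the arm contrast has variance 4σ²(1 - ρ)/n under difference-in-differences and 2σ²(1 - ρ²)/n under baseline adjustment. The ratio is (1 + ρ)/2: 35% lower at ρ = 0.3, 25% lower at ρ = 0.5, and never higher for ρ below 1.

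**The case against.** The strongest reply is that the interaction is a valid test. Under randomisation it is unbiased, nothing here inflates its type I error, and with a correlation of about 0.5 or more at a 39% baseline the stated 80% is roughly met or exceeded. That stands, and it means the documents do not fix a shortfall of any particular size. A reader might infer that power is simply 40-65%. That range needs a correlation of about 0.3 or less, or a high baseline, and the article states neither.

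A reader might also infer that baseline IPV sits near the ceiling, say 90%. The entry questions (Informed consent and enrollment) admit women who feel unsafe or threatened without any recent physical or sexual IPV, so that is not established. A rate above 39% is a fair inference, because 39% is a national lifetime figure and these women are selected on recent IPV or fear.

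A third tempting inference is that site will be handled by cluster-robust errors or a random effect on three sites. The sentence on accounting for site names no such method, and fixed site effects satisfy it equally well.

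The figures above also cover binary IPV only. IPV is to be analysed as a continuous score too, and no power is stated for that. Finally, changing a declared primary model after data collection is more than a matter of wording. Interim IPV prevalence was reviewed by the investigative team (end of Background), so the timing of any change has to be documented.

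**Conclusion.** The mismatch holds: the power section describes a different test from the one declared primary, and both stated power figures reproduce only for that other test. The size of the gap is conditional. At 175 per arm and a 39% baseline it runs from about 50% power at zero correlation to no loss at about 0.5 and a gain above that. With 149 per arm and the same effect, power is about 6-8 points lower up to a correlation of 0.5. If baseline IPV is 70% or more, which the entry criteria make plausible but do not prove, power stays below 80% on both scales. That bound assumes the plan's own follow-up rates of 39% and 25%.

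The case for baseline adjustment of the continuous outcomes does not rest on the unknown correlation, since it is at least as precise for any value below 1. It cannot apply to safety preparedness.

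**What to change.** - **Outcomes measured at baseline and 3 months:** make the primary model the 3-month outcome on arm, the baseline value of the same outcome, and site (the stratification factor) as a fixed effect. A longitudinal model with a common baseline mean is an alternative. Report the arm contrast with its confidence interval, and keep the interaction model as a sensitivity analysis.
- **Safety preparedness:** specify a site-adjusted comparison of arms on the post-intervention score.
- **Record:** document the change, with its date, as made before any unblinded outcome analysis.
- **If difference-in-differences stays primary:** restate the power for the interaction over a range of baseline rates and correlations, as in the tables above, in place of the single 80%.

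No new data are needed, since the survey is given at baseline and at 3 months. The cost is an amendment to the analysis text and a transparent account of when and why it was made. Restating the power will not enlarge the sample, but it tells readers how to weigh a non-significant interaction.
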